### 2.7. Missing Data Handling in the Analysis

In general, missing data will not be imputed for safety, demographic, or baseline characteristic variables; analyses will be based solely on observed data. For the primary endpoint and other time-to-event secondary endpoints, missing outcome information due to loss to follow-up or withdrawal of consent prior to an event will be addressed through right-censoring at the date of the last adequate disease assessment. These analyses assume that missingness is consistent with a missing at random (MAR) mechanism and that censoring is non-informative, such that the censoring process is independent of the event process conditional on the information available.

### 2.8. Methods for Any Additional Analyses

To evaluate the consistency of the treatment effect across the study population, subgroup analyses will be performed for the primary endpoint (3-year PFS) and key secondary endpoints. As this is a single-arm study, these analyses will be descriptive and exploratory. Point estimates and 95% confidence intervals will be presented for each subgroup. No formal hypothesis testing for interaction is planned. The prespecified subgroups based on baseline characteristics include:

Demographics: Age (e.g., ≤40 years vs. >40 years), sex (male vs. female);

Clinical Characteristics: Presence or absence of LNM in LR patients.

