### 2.3. Patient Stratification and Treatment

Stratification is performed in two steps to define the low- and high-risk categories.

The first is based on the TMTV value at baseline (low or high) and presence/absence of modified EORTC (mEORTC) criteria, in which the classical bulky disease (defined as a nodal mass larger than 10 cm) is replaced by a “large nodal mass” (LNM) of 5–10 cm in diameter (Figure 1). The second step is after the second chemotherapy cycle and is based on PET-2 results.

The low-risk (LR) group is defined by a baseline TMTV < 84 mL and negative interim PET-2 (Deauville scale; DS: 1–3). Within this category, patients are further split into two more categories: group 1a—patients without mEORTC risk factors that receive two chemotherapy cycles only, and group 1b—patients with at least one risk factor according to the mEORTC criteria that receive four chemotherapy cycles (Figure 2). The ABVD chemotherapy includes doxorubicin 25 mg/m^2^, bleomycin 10 IU/m^2^, vinblastine 6 mg/m^2^, and dacarbazine 375 mg/m^2^, administered intravenously on days 1 and 15 of each 28-day cycle.

The HR group includes patients with either a positive PET-2 (DS 4–5, group 3a) and/or baseline TMTV ≥ 84 mL (group 3b). Both patient subsets receive a “triple therapy,” consisting of four chemotherapy cycles, INRT at either 20 or 30 Gy depending on the absence or presence of baseline mEORTC risk factors, respectively, followed by Nivolumab maintenance administered every two weeks at a dose of 240 mg intravenously over 30 min for up to one year, for a maximum of 24 doses (Figure 2). This duration was selected based on the CheckMate 205 and KEYNOTE-087 studies [12,13]. The newly diagnosed advanced-stage HL patients (CheckMate 205 study, group D) received up to 16 doses of nivolumab (4 doses of monotherapy and 12 in combination with AVD chemotherapy). The relapsed/refractory patients received nivolumab up to disease progression or unacceptable toxicity, with a possibility of treatment discontinuation in group C for patients with CR for 1 year. In both cases, acceptable CR rate and duration were achieved. The KEYNOTE-087 data show that 1 year of PD-1 blockade is associated with sustained remissions [14]. Recognizing that the optimal duration of anti-PD-1 therapy in this setting remains unknown, this study will explore correlations between treatment duration, toxicity, and outcomes to inform future trials.

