### 2.5. Sample Size

The sample size calculation was based on the following assumptions: the anticipated 3-year progression-free survival (PFS) rate for stage I–IIA non-bulky eHL patients with a negative PET-2, treated with CMT, is 94% [6]; the expected 3-year PFS for PET-2-negative patients with similar clinical characteristics, treated with chemotherapy alone comprising two to four courses of chemotherapy, ranges between 87% and 93%, as reported in three prospective and one retrospective clinical trials, despite variations in patient characteristics and treatment intensity [6,7,8,28].

The expected 3-year PFS for PET-2-negative patients with TMTV < 84 mL treated with chemotherapy alone is anticipated to be at least 90%. In this context, a one-sample non-inferiority design was employed to calculate the sample size required to test whether the proportion of low-risk eHL patients, treated with chemotherapy alone, alive and disease-free at 3 years, is non-inferior to that of patients treated with CMT. For the non-inferiority assessment of the primary endpoint, we assumed an expected true response proportion of 90%. The non-inferiority historical reference value was set at 95%, reflecting the historical outcome of CMT reported in trials such as RAPID and H10, with an absolute non-inferiority margin of 10 percentage points; thus, non-inferiority would be concluded if the response proportion in the study population exceeds 85%.

To define the sample size of patients to be enrolled, we used a one-sided type I error of 0.20 and type II error of 0.20 (80% power). “The one-sided α of 0.20 was prespecified because the study was designed as an exploratory Phase 2 screening trial, in which minimizing false-negative findings was prioritized over controlling false-positive findings, consistent with the recommendations of Rubinstein et al.” [29].

A total of 102 low-risk (defined by a low MTV and a negative PET-2) eHL patients should be enrolled to exclude a difference between the true proportion and the comparison value of at least 10%. Considering an expected 75% of patients with a negative PET-2 and low TMTV, and a drop-off rate of 15%, 160 patients had to be enrolled in the trial.

In the exploratory phase 2 setting, a one-sided α = 0.20 was chosen because the potential harm of a false negative result (failing to recognize an effective treatment) is considered more significant than that of a false positive result (proceeding to confirmatory testing) [29].

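### The pooled low-risk primary mixes a two-cycle and a four-cycle regimen, and the one clinical subgroup named, large nodal mass, does not separate them

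*Protocol article*

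**What the plan says.** Section 2.3 splits the LR group by mEORTC status. Group 1a is "patients without mEORTC risk factors that receive two chemotherapy cycles only" and group 1b is "patients with at least one risk factor according to the mEORTC criteria that receive four chemotherapy cycles". The same section makes LNM (5–10 cm) one of the mEORTC factors, in place of classical bulk.

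Sections 2.5 and 2.6 treat LR patients as one population. There is one expected 3-year rate (90%), one historical reference (95%), one margin (10 points) and one sample size: "A total of 102 low-risk (defined by a low MTV and a negative PET-2) eHL patients should be enrolled". There is also one decision: the lower one-sided 80% bound for 3-year PFS must exceed 85%.

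Section 2.8 plans subgroup estimates to look at consistency of the effect. It lists age, sex and "Clinical Characteristics: Presence or absence of LNM in LR patients". Group 1a versus 1b is not listed. All subgroup estimates are labelled descriptive and exploratory, with 95% confidence intervals and no interaction test.

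The Discussion says that a positive result will reflect the algorithm as a whole. It also speaks of radiation-free regimens, in the plural, being comparable with combined-modality treatment, and of a case for revising guidelines.

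**The concern.** Within LR, the variable that fixes the treatment is mEORTC status. LNM is only one component of it, and the tie runs one way: LNM present implies four cycles, but LNM absent implies either two or four.

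Two consequences follow. First, a difference between LNM strata cannot be assigned to mass size or to cycle number. The Introduction reports LNM as strongly adverse (hazard ratio 3.78 in the RAPID reappraisal). An adverse effect of LNM and an effect of fewer cycles in the other stratum could therefore offset each other and look like consistency. Second, no listed estimate isolates the two-cycle patients. If they did worse than the 85% limit, the pooled rate could still pass, and the LNM-negative stratum would show only a diluted version of the shortfall. A reader who wants to apply the result to two-cycle patients would have no listed estimate to consult.

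**Working it through.** **Reproducing the plan's figure.** Inputs from section 2.5: one-sided alpha 0.20, power 0.80, expected rate 0.90, limit 0.95 − 0.10 = 0.85. With the variance taken at the expected rate,

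n = (0.8416 + 0.8416)² × 0.90 × 0.10 / (0.90 − 0.85)² = 102.0.

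Total enrolment: 102 / 0.75 / (1 − 0.15) = 160. Both match, so the sample size is not in question.

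**The decision rule as a count.** Take n = 102 with complete follow-up, so that the Kaplan–Meier estimate is a proportion and the Greenwood error is binomial.
- 12 events: 90/102 = 88.24%; bound = 0.8824 − 0.8416 × √(0.8824 × 0.1176/102) = 85.55%, which passes.
- 13 events: 89/102 = 87.25%; bound = 84.48%, which fails.

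The rule therefore passes with at most 12 events. Its exact type I error at 85% is 0.223 and its power at 90% is 0.782.

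**Can the pooled test pass with group 1a below 85%?** The article gives no 1a share and no rates by group, so both are assumed here: a share of 30% to 70%, true 3-year PFS of 82% in 1a and 95% in 1b. Pooled rate = (n1a × 0.82 + n1b × 0.95)/102. The probability of passing is P(events in 1a + events in 1b ≤ 12), from the exact convolution of two binomials.

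| 1a share | n 1a / 1b | Pooled true rate | P(non-inferiority declared) |
|---|---|---|---|
| 30% | 31 / 71 | 91.0% | 0.88 |
| 40% | 41 / 61 | 89.8% | 0.76 |
| 50% | 51 / 51 | 88.5% | 0.61 |
| 60% | 61 / 41 | 87.2% | 0.45 |
| 70% | 71 / 31 | 86.0% | 0.31 |

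With 1a at 80% the probabilities are 0.83, 0.67, 0.48, 0.31 and 0.18.

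**What would the LNM-negative stratum show?** It contains all of 1a plus m patients of 1b who qualify through another factor. Assume that 30% to 70% of 1b is LNM-negative and that those patients have a rate of 95%. Expected rate = (n1a × 0.82 + m × 0.95)/(n1a + m).
- 30% share: m = 21 gives (25.42 + 19.95)/52 = 87.3%; m = 50 gives (25.42 + 47.50)/81 = 90.0%.
- 50% share: m = 15 gives (41.82 + 14.25)/66 = 85.0%; m = 36 gives (41.82 + 34.20)/87 = 87.4%.
- 70% share: m = 9 gives (58.22 + 8.55)/80 = 83.5%; m = 22 gives (58.22 + 20.90)/93 = 85.1%.

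The true 82% appears as 83.5% to 90.0%. Dilution is worst where 1a is small, which is also where the pooled test passes most often.

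**Precision of a separate 1a estimate.** The two-sided 95% half-width at a true 90% is 1.96 × √(0.09/n): 10.6 points at n = 31, 8.2 at n = 51, 7.0 at n = 71.

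**The case against.** The strongest reply is that pooling is a disclosed choice. The trial tests a risk-adapted strategy, the assumed rate in section 2.5 already draws on studies of two to four courses taken together, and the Discussion ties a positive result to the whole algorithm. This stands. Pooling is not an error, and no rule in the article declares the two-cycle regimen non-inferior.

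Section 2.8 introduces its list as one that includes these subgroups, and the full protocol or analysis plan may add 1a and 1b. That also stands as a caution. The point therefore rests on what is stated: LNM is named across all LR patients, and that contrast is confounded by construction.

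The scenario is invented. Patients without risk factors might be expected to do better, and nothing in the article supports 82% against 95%. This stands too; fewer cycles could reverse the order, but the table shows only that masking is possible.

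A reader might infer that a failing two-cycle regimen could be declared non-inferior without anyone seeing it. The article does not support that. The claim would be for the LR group as a whole. All 1a patients fall in the LNM-negative stratum, so a shortfall there is diluted, not invisible. At a 1a share of 60% to 70%, the pooled test fails more often than not in the scenario above.

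A reader might also want the pooled claim withheld whenever the 1a estimate is below 85%. Such a gate is uncalibrated. With 41 patients in 1a, it would miss a true 82% about 38% of the time and would trigger at a true 90% about 11% of the time. A matching split of the high-risk group into 3a and 3b does not follow either, because both receive the same triple therapy.

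**Conclusion.** The point holds as one of analysis choice and interpretation. The primary pools two regimens, and the named LNM subgroup neither isolates the two-cycle group nor separates mass size from cycle number. Under the assumed rates of 82% and 95%, pooled non-inferiority would be declared with probability 0.88 at a 30% share of 1a and 0.61 at a 50% share, falling to 0.31 at 70%. These figures rest on an assumed share, assumed rates and complete follow-up, and are not a forecast. The sample size of 102 stands. Nothing here bears on which number of cycles is right.

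**What to change.** Before the 3-year analysis:

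1. Prespecify descriptive 3-year LR PFS with two-sided 95% confidence intervals separately for groups 1a and 1b.
2. Evaluate LNM within group 1b only, where all patients are assigned four cycles.
3. State with the primary result, in line with the Discussion, that the pooled conclusion applies to the risk-adapted LR strategy and does not by itself establish non-inferiority of either regimen.

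The cost is two extra Kaplan–Meier estimates. The mEORTC breakdown is collected at screening (section 2.4) and already determines treatment, so no new data or patients are needed, and follow-up is still ongoing. The downside is limited precision: the 1a and 1b estimates remain exploratory and cannot support a non-inferiority claim of their own. A separately powered test in each group on the same inputs would need 2 × 102 = 204 LR patients and 204/0.75/0.85 = 320 enrolled, assuming an even split. That is not proposed here.

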### 2.9. Toxicity and Safety Monitoring

All patients who have received at least one dose of the study treatment will be evaluable for toxicity from the time of their first drug administration. When toxicity occurs, it should be graded according to the National Cancer Institute Common Toxicity Criteria, version 5.0. Any clinically significant abnormality persisting at the end of the study will be followed up by the investigator until resolution or until reaching a clinically stable endpoint.

The safety parameters are evaluated by an external Independent Data Safety and Monitoring Committee (IDSMC) during two meetings (2 months after the first 40 patients enrolled or earlier if any emerging safety signals appear and 2 months after the next 40 patients enrolled or earlier if any emerging safety signals appear). Following each meeting, the IDMSC prepares a report and may recommend changes in the study conduction.

The interim analysis was planned after enrollment of the first 50 patients. Recruitment will be stopped if the incidence of second HL relapses among LR patients exceeds the prespecified threshold (10 ± 5%). No early stopping boundary for efficacy was planned because this exploratory non-inferiority study is intended to complete the prespecified recruitment and follow-up to estimate the primary endpoint with the planned precision.

## 3. Discussion

HL, especially in early stages, remains a model of success in oncology, with survival rates around 90% [31]. Nevertheless, patients with eHL still demonstrate heterogeneity in treatment response, ranging from an extremely favorable subgroup that can be cured with chemotherapy alone to an extremely unfavorable subgroup that does not respond to standard CMT and subsequent lines of treatment [31]. Moreover, since the turn of the millennium, several novel prognostic factors derived from functional imaging and molecular biology have emerged to guide treatment intensity and to detect minimal residual disease at the end of therapy. The RAFTING trial is the first prospective study in eHL specifically designed to address both polarized patient populations. It proposes a highly individualized treatment strategy using easily available tools aimed at maximizing efficacy while minimizing toxicity.

To stratify patients with variable prognosis, baseline TMTV, mEORTC criteria, and PET-2 results were applied. All of them were introduced based on the results of previous studies, including studies involving patients with characteristics similar to those of the RAFTING trial, often including a radiation-free treatment arm, which clearly showed that 60% of early favorable HL patients could be cured with chemotherapy alone.

Finally, data from these studies also demonstrated that approximately 30% of PET-2-negative patients who relapsed in initially involved nodes were effectively salvaged with RT alone. These observations, together with the excellent results achieved with anti-PD1 monoclonal antibodies at various treatment stages in HL provided the rationale for introducing a triple treatment in the HR group and a rescue approach with INRT and nivolumab maintenance in the LR group in case of limited relapse. This strategy may allow avoidance of the toxicity associated with HDCT and auto-HCT. The integration of delayed RT and nivolumab in patients with limited relapse in LR group ensures that even those with suboptimal initial responses have access to potentially curative interventions.

The sample size calculation was based on the proportion of patients cured with RFT in previous prospective studies. Consequently, the primary endpoint of this phase 2 prospective, single-cohort clinical trial is the 3-year PFS in the low-risk group of patients treated with chemotherapy alone. The non-inferiority design provides a rigorous framework for determining whether radiation-free chemotherapy regimens can achieve efficacy comparable to conventional CMT within a 10% margin in this subgroup. The 10% non-inferiority margin was chosen based on statistical reasoning, clinical judgment, and the feasibility of implementing the study plan, balancing the risk of reduced disease control against the potential long-term benefit of omitting radiotherapy. A narrower margin, such as 5%, would have required a substantially larger sample size, approaching that of a confirmatory trial. Therefore, the present study is intended to exclude clearly unacceptable loss of efficacy and to inform the design of a subsequent phase 3 trial using a more stringent margin. We also referred to prior Hodgkin lymphoma trials that used a 7–10% non-inferiority margin to define clinically meaningful differences in efficacy (RAPID trial—7%, EORTC/LYSA/FIL H10—10%) [6,7].

Equally important is the main secondary endpoint, the 3-year EFS in all groups of patients, which will allow estimation of the proportion of patients who fail the planned treatment. Thus, the limited relapse in LR patients treated with delayed INRT and nivolumab is not considered as an event. The events defining the true failures of planned treatment include only extended relapse at any time or any relapse including limited relapse after completing the triple treatment.

The RAFTING trial is also the first prospective study to evaluate the role of cfDNA in eHL. By investigating cfDNA as a predictor of impending relapse, the trial aligns with the increasing interest in liquid biopsies as a non-invasive monitoring tool. This approach has the potential to enable earlier interventions in patients at risk of relapse and may ultimately improve long-term outcomes. Subsequent studies could refine cfDNA thresholds, assess cost-effectiveness, and evaluate the applicability of this approach in other lymphoma subsets.

Nonetheless, the protocol faces important challenges. The complexity of the study design may lead to deviations in treatment or procedures. Another very important limitation is the single-arm design and reliance on comparison with a historical control. Such comparisons may be influenced by temporal changes in chemotherapy application, supportive care, imaging and RT techniques, and other aspects of clinical practice. However, the standard first-line treatment of eHL, based on chemotherapy with PET-adapted strategies, has remained largely unchanged over the past two decades, with stable results, including a 3-year PFS of 95%. Improvements in supportive care are unlikely to have substantially influenced PFS. The influence of improvements in imaging and RT techniques cannot be ruled out in a single-arm study with a historical comparator. We selected the RAPID trial as the principal historical benchmark because it represents a well-characterized PET-adapted cohort with similar, although not identical, eligibility criteria and RT technique (INRT). In addition, response assessment in the comparator studies was performed using blinded independent central review, reducing variability in PET interpretation, as in the RAFTING study. Nevertheless, advances in PET/CT acquisition, reconstruction algorithms, scanner performance, and staging procedures over time may have influenced patient classification and outcome assessment. Therefore, comparisons with historical controls should be interpreted with caution, and our findings require confirmation in prospective randomized or contemporaneous comparative studies. Another limitation of the study is related to future implementation of the study results, related to potential variability in imaging interpretation in the real-world setting, particularly regarding the assessment of PET-2 and baseline TMTV. The central review process has been implemented to minimize this risk in the study. Moreover, the BICR of a given test is needed when the study endpoint depends directly on this test [23]. The real-world application of these criteria may lead to inconsistencies across treatment centers. Similarly, the use of cfDNA as a biomarker, although highly promising, remains exploratory, and definitive conclusions may be limited by inherent variability in assay sensitivity and specificity. Additional challenges relate to the details of the treatment protocol. The initially planned schedule of 24 nivolumab doses may prove difficult to achieve in all patients, and available data suggest that shorter treatment courses might still provide adequate disease control in this setting.

Future validation against independent contemporary cohorts would provide additional reassurance regarding the reproducibility and generalizability of the present findings. Sensitivity analyses exploring the impact of alternative comparator populations or analytical assumptions could further evaluate the robustness of the results. However, these analyses are beyond the scope of the current exploratory phase 2 study.

We would like to emphasize that any positive result of the study will reflect the whole study algorithm, not the separate checkpoint of treatment blocks.

The recruitment of patients was completed in October 2023, and the target sample size was achieved. All patients finished the planned per-protocol treatment. Clinical follow-up is ongoing according to the study protocol.

To conclude, if the RAFTING trial confirms the efficacy of RFT in low-risk patients defined with new proposed tools, it will provide strong arguments for revising current treatment guidelines. Incorporating TMTV and mEORTC criteria together with PET-2 into risk stratification could become a cornerstone of HL management, supporting a more individualized approach with reduced long-term toxicity. If successful, the study findings will have significant implications for the management of HL, particularly by reducing the incidence of long-term complications such as secondary malignancies and cardiovascular disease.

All information generated by the RAFTING study is owned by the study sponsor, the Medical University of Gdansk. The latter will have the discretion of committing to the Principal Coordinating Investigator or his delegates to disseminate the results of the study to the medical community. All information and results derived from this trial will be considered confidential, at least until such time as appropriate analysis and verification have been concluded by the sponsor, the coordinating investigators, and the trial statistician.

The results of the study will be disseminated through publication in peer-reviewed scientific journals and presentation at national and international scientific conferences. The findings will be reported in accordance with relevant reporting guidelines and will be published irrespective of the nature or direction of the results.

